The intersection of HIV and trauma highlights the importance of integrated mental health treatment and HIV care, particularly in a setting like South Africa where mental health services are limited, and women are both more likely to be living with HIV [33] and face overlapping epidemics of gender-based violence and sexual trauma [34]. Specifically, effective interventions are needed that address the combined stress of trauma and HIV among WLH to improve psychological and clinical outcomes from the outset of ART initiation [35, 36]. There is strong reason to expect that reducing traumatic stress would decrease avoidance [37, 38] and increase care engagement [1], thus increasing viral suppression. Although some interventions aimed at treating sexual trauma among WLH in order to improve care engagement have been developed [1, 37–39], and treatments aimed at addressing IPV in this population have shown promise [40], we are unaware of any full-scale trials that test the effectiveness and examine the underlying mechanisms of change of a trauma-related coping intervention to improve or maintain viral suppression and related clinical outcomes.

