ART initiation represents a unique window of opportunity to enhance motivation and address the negative effects of trauma on avoidant coping behaviors [41, 42] to increase care engagement and interrupt losses that occur throughout HIV care cascade [43, 44]. In 2016, we conducted a pilot trial of ImpACT, a task-shared intervention that sought to improve mental health and clinical outcomes among WLH with sexual trauma histories in South Africa by addressing coping with HIV and trauma and therefore increasing adherence to anti-retroviral therapy (ART) [45, 46]. The ImpACT intervention was based on *Living in the Face of Trauma* (LIFT), a CDC—and SAMHSA—evidence-based intervention for adults living with HIV with histories of childhood sexual abuse in the United States (US). LIFT significantly reduced incidents of unprotected sex [47], substance use [48], and traumatic stress symptoms [37]. Notably, reductions in traumatic stress were fully explained by reductions in avoidant coping. ImpACT was adapted and refined to become ImpACT + and is the intervention evaluated in this trial. Task-shared for delivery by a non-specialist, ImpACT + shows promise to address the synergistic stress of sexual trauma and HIV and the multifaceted needs of WLH in South Africa. In this trial, we aim to prove the efficacy of this acceptable, feasible, and culturally relevant intervention to improve clinical outcomes.

The paucity of culturally relevant evidence-based mental health treatments is accompanied by two significant barriers to scalability: (1) the shortage of trained mental healthcare providers across low resource settings [49] and (2) uncertainty as to the best setting for delivery [50]. There is increasing evidence that culturally adapted mental health interventions delivered by nonspecialists in LMICs have potential to treat depression, trauma, and effects of intimate partner violence (IPV) among WLH [40, 45, 51]. Care providers in LMICs emphasize the need for mental health interventions that can be integrated into chronic care systems and strengthen the healthcare system [52]. Integrating a targeted, task-shared trauma intervention into HIV care may help address the limited capacity of the mental health care system to identify and treat women with traumatic stress.

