### Objectives {7}

The primary objective of this trial is to determine the effectiveness of ImpACT + on viral load suppression by reducing avoidant coping and traumatic stress among WLH with sexual trauma in Cape Town, South Africa.

The specific objectives are:To determine the effectiveness of ImpACT + , compared to adapted problem-solving therapy (PST), on clinical outcomes over a 12-month period among WLH with sexual trauma who are initiating ARTTo examine underlying mechanisms of change by evaluating the degree to which improvements in mental health and coping mediate intervention effects on primary (viral suppression) and secondary outcomes (adherence and care engagement)To explore the scalability of ImpACT + , guided by the Consolidated Framework for Implementation Research (CFIR) [53], to better understand facilitators and barriers to full-scale implementation

Our primary hypothesis is that a greater proportion of ImpACT + participants will be virally suppressed (primary outcome), adherent, and engaged in care (secondary outcomes) at 12 months compared to PST participants. Our secondary hypothesis is that over time, ImpACT + participants, as compared to PST participants, will report greater reductions in (1) traumatic stress and (2) avoidant coping, which, in turn, will lead to (causally mediated) improvements in ART adherence, care engagement, and viral load (VL) at 12 months.

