### Outcomes {12}

The primary outcome measure is viral suppression at 12 months, determined by HIV viral copies per milliliter of blood. Viral suppression will be reported as a dichotomous variable with the threshold for viral suppression defined as < 50 copies/mL, as determined by the Abbott Alinity assay (Sensitivity Limit of Detection 20 copies/mL).

The following secondary outcome measures will be assessed at baseline, 4, 8, and 12-month timepoints:ART adherence:◦ Dried blood spots measuring levels of tenofovir-diphosphate (TFV-DP) (at 12 months)◦ Medical record abstraction of pharmacy visits and pharmacy refill data◦ Adapted Adult AIDS Clinical Trials Group self-report measure of adherence [74, 75]HIV care engagement (medical record abstraction):◦ Missed visits (# of monthly visits missed and binary indicator of any missed monthly visit)◦ Visit adherence (proportion of visits kept)◦ Gaps in care (whether > 90 days have elapsed between visits)◦ Visit constancy (# of 90-day intervals with > 1 completed visit).◦ Mental health mediators will be assessed by the following measures (all timepoints):Post-Traumatic Stress (PTSD Checklist-Civilian version for the DSM-5 (PCL-5) [76]Coping [45], adapted from [77–81].

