## Statistical methods

### Statistical methods for primary and secondary outcomes {20a}

To assess intervention effects on the primary outcome (viral suppression), we will compare the proportion of participants achieving HIV viral suppression at 12 month follow-up across study conditions by estimating a risk ratio and obtaining confidence intervals using robust error variances with a modified Poisson model and log link [83]. We will similarly obtain risk ratio estimates to assess intervention effects on the secondary outcomes (i.e., measures of ART adherence and care engagement) using the modified Poisson approach appropriate distribution and link function based on the outcome examined.

To examine the underlying mechanisms of the intervention effects on primary and secondary outcomes at 12 months, we will evaluate the effects of ImpACT + , compared to PST, on hypothesized mediators (e.g., levels of traumatic stress and avoidant coping). Our analytic approach will incorporate the appropriate distribution and link function depending on the distribution of these mediators. We will then examine the effect of both mediators on viral load. If the product of these two paths is greater than zero, this will serve as evidence of mediation [84]. The same approach will be utilized to evaluate the degree to which changes in traumatic stress and avoidant coping mediate intervention effects on secondary outcomes (ART adherence and care engagement).

Finally, qualitative data will be analyzed using a thematic analysis approach [85]. Memos will be written for each transcript to synthesize the emerging themes across the CFIR domains. Themes will be identified via consensus discussion after independent review of transcripts and textually coded using NVivo and/or ATLAS.ti software by multiple coders. Data display matrices will be used to examine commonalities and differences across informants [86]. A diagrammatic visual, overlaid on the CFIR framework [53] will highlight the potential barriers and facilitators to full-scale implementation.

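### The causal mediation hypothesis rests on a mediator-to-outcome step that randomisation does not protect, with no stated adjustment and no stated mediator visit

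*Protocol article*

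**What the plan says.** The secondary hypothesis in Objectives {7} is causal. Reductions in traumatic stress and avoidant coping are expected to act on the clinical outcomes, "which, in turn, will lead to (causally mediated) improvements in ART adherence, care engagement, and viral load (VL) at 12 months".

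Statistical methods {20a} gives the method, introduced with "To examine the underlying mechanisms of the intervention effects on primary and secondary outcomes at 12 months". The effect of arm on each mediator is estimated first. Next: "We will then examine the effect of both mediators on viral load". The decision rule follows: "If the product of these two paths is greater than zero, this will serve as evidence of mediation". The same approach is then applied to adherence and care engagement.

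On timing, Outcomes {12} states: "Mental health mediators will be assessed by the following measures (all timepoints"), that is, at baseline and at 4, 8 and 12 months. The methods section does not say which of these visits supplies the mediator. The only covariates mentioned for any model are predictors of loss to follow-up, used in a sensitivity analysis for missing data (section {20c}).

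**The concern.** Randomisation makes the arm-to-mediator comparison fair. It does nothing for the comparison of women with low and high stress or avoidance within an arm. Baseline trauma severity, baseline coping and initiation status (new initiator, restarter or defaulter) could each influence both the follow-up mediator and viral suppression. If so, the second path picks up an association that is not an effect, and the product turns it into apparent mediation.

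Timing adds a second route to error. A month-12 PCL-5 score taken alongside the month-12 viral load has no time order. Missed visits, gaps in care and 90-day visit counts accumulate over follow-up, so a late mediator value could be a consequence of the outcome it is meant to explain.

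The Discussion says a mediation result would strengthen the case for putting mental health services into primary care. A confounded result would feed that argument while showing only that less distressed women have better HIV outcomes.

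**Working it through.** **The plan's own figure.** The article gives no figure for the mediation analysis. Its one calculation is for the primary outcome: 57% versus 73%, two-sided 5%, 80% power, 350 randomised, 80% retained.

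- Retained per arm: 350 × 0.80 / 2 = 140.
- Required n per arm = [1.960·√(2 × 0.65 × 0.35) + 0.842·√(0.57 × 0.43 + 0.73 × 0.27)]² / 0.16² = (1.322 + 0.560)² / 0.0256, which gives 139.
- Inflated: 139 / 0.80 = 174 per arm, 348 in total, against 350 stated. Power with 140 per arm is 0.805. The figure reproduces, and this point does not touch it.

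**What the product estimates when nothing is mediated.** The following are assumptions, not in the documents. Arm X shifts the mediator M by a = −0.4 SD. A shared factor U loads c on the baseline mediator, c on the follow-up mediator and −c on the latent outcome. All are scaled to variance 1 within arm. M has no effect on the outcome. The outcome is coded as suppression, so the hypothesised route gives a positive product.

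- Outcome on arm and M, unadjusted: the coefficient of M is b = −c². The product is a·b = 0.4c², while the true value is 0. For c = 0.3, 0.45 and 0.6 this is 0.4 × 0.09 = 0.036, 0.4 × 0.2025 = 0.081 and 0.4 × 0.36 = 0.144 latent SD.
- Adding the baseline mediator: b = −c²/(1 + c²). The share of bias removed is c²/(1 + c²) = 0.09/1.09 = 8%, 0.2025/1.2025 = 17% and 0.36/1.36 = 26%.
- Change from baseline as mediator: U cancels because it loads equally at both times, so b = 0.
- Adjusting for U itself: b = 0.

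**How often mediation is falsely found.** Simulation with 140 per arm and both paths required to be significant at 5%:

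- Binary suppression at 57% and 73%, follow-up levels: 20%, 67% and 91% for c = 0.3, 0.45 and 0.6.
- Same, with an arm effect of 0.3 SD: 14%, 53% and 70%.
- Continuous outcome, follow-up levels: 31%, 84% and 92%.
- Change scores with a stable confounder: 3% to 4%.
- Binary suppression, adjusted for the baseline mediator only: from 18% to 87%.
- Adjusted for the shared factor itself, measured without error: 4% to 5%.

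**The rule taken literally.** If a positive point estimate is enough, a separate simulation (0.3 SD arm effect, binary suppression, no mediation) gives a positive product in 50% of trials with no confounding at all, and in 87% at c = 0.3 and 97% at c = 0.4. Requiring the 95% interval to lie above zero gives 1%, 13% and 37%. An interval is therefore needed, but it does not cure confounding.

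**The case against.** The strongest reply is that a journal article may leave the mediator visit and the covariate list to an analysis plan that is not shown. The text never says the outcome model is unadjusted, and measuring mediators at every visit makes correct ordering possible. That is fair as far as silence goes. The point survives because the article itself fixes a causal hypothesis, an estimation route and a decision rule, and as stated these do not match.

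The article also speaks of changes in the mediators when it turns to the secondary outcomes, and of reductions in the hypothesis, although it says levels for the arm-to-mediator step. If change scores are meant and the confounder is stable, the false-positive rate nearly vanishes. This stands, and it is why the size is an illustration only. Unequal or time-varying confounding would bring bias back.

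Three stronger readings are not supported:

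- A reader might infer that the protocol gives conflicting mediator orders, since the background says "reducing traumatic stress would decrease avoidance" and, of an earlier US trial, that "reductions in traumatic stress were fully explained by reductions in avoidant coping". Both are background statements and are compatible with a reciprocal relation. The hypothesis lists the two mediators side by side, and the methods fix no order.
- A reader might infer separate products that double-count. The methods refer to both mediators, which can equally mean one joint model.
- A reader might infer that every adjustment variable is already collected. Section {18a} places viral load sampling at follow-up visits. The Abstract's mention of biological and behavioural assessment at baseline does not settle whether a baseline viral load exists.

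**Conclusion.** The concern holds for the secondary, mechanistic hypothesis. The stated product-of-paths method leaves the mediator-outcome path open to confounding and permits a mediator measured with, or after, the outcome. It does not support the word *causally*.

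The possible size is large but rests on assumptions: about 20% to 91% false mediation for binary suppression using follow-up levels, 3% to 4% with change scores and a stable confounder, and only a partial reduction from adjusting for the baseline mediator alone. The documents give no values for the loadings or for the arm effect on the mediators, so none of these is an estimate of the bias in this trial. The randomised comparison of viral suppression stands as planned. This should be corrected before the mediation analysis is run.

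**What to change.** In the analysis plan, before the mediation analysis:

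1. Take the mediators at 4 or 8 months, with the other visit as a sensitivity analysis, and the outcome at 12 months. Count care-engagement outcomes from the mediator visit onward.
2. Include arm, baseline PCL-5, baseline coping and the randomisation strata (initiation status, clinic, pregnancy) in both the mediator and the outcome models. Add baseline viral load only if it can be obtained from records.
3. Report the joint indirect effect through both mediators with a confidence interval. It does not depend on which mediator comes first. Replace the greater-than-zero rule with that interval.
4. Add a sensitivity analysis for unmeasured mediator-outcome confounding, and drop *causally* if the result is not robust to it.

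The cost is plan wording and code: PCL-5 and coping are measured at baseline, and the strata are recorded at randomisation. There is a real trade-off in the choice of visit. The maintenance check-ins start after the 4-month assessment, so a 4-month mediator misses them entirely and an 8-month mediator captures only part. Counting care engagement from the mediator visit also changes what those outcomes measure in this analysis.

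### One rule, a path product greater than zero, is used for all mediation outcomes, but the hypothesised sign differs between them and the rule as worded has no interval or test

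*Protocol article*

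**What the plan says.** All references are to the protocol article.

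- **First path.** Statistical methods {20a} estimates the effect of arm on the "hypothesized mediators (e.g., levels of traumatic stress and avoidant coping").
- **Second path.** The same paragraph continues: "We will then examine the effect of both mediators on viral load".
- **Decision rule.** "If the product of these two paths is greater than zero, this will serve as evidence of mediation". No interval, test or significance level is attached to the product.
- **Reuse of the rule.** "The same approach will be utilized to evaluate the degree to which changes in traumatic stress and avoidant coping mediate intervention effects on secondary outcomes", that is, ART adherence and care engagement.
- **Hypothesis.** Objectives {7} expects that ImpACT+ participants "will report greater reductions in (1) traumatic stress and (2) avoidant coping", leading to "causally mediated) improvements in ART adherence, care engagement, and viral load (VL) at 12 months".
- **Mediated outcome.** The second specific objective in Objectives {7} is about how far mental health and coping "mediate intervention effects on primary (viral suppression) and secondary outcomes (adherence and care engagement"). Outcomes {12} fixes the primary outcome as binary at 50 copies/mL: "Viral suppression will be reported as a dichotomous variable".
- **Coding of secondary outcomes.** Outcomes {12} lists some care-engagement measures where higher is worse (missed visits, gaps in care) beside others where higher is better (visit adherence, visit constancy).

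**The concern.** The sentence fixes a criterion; it does not merely leave a detail open. Two things about it need attention.

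**Sign.** The product of two paths takes its sign from how the mediator and the outcome are coded. A single rule in one direction works only if every outcome is coded the same way, and here they are not. For an outcome where higher is worse, the rule treats the hypothesised mechanism as no evidence and treats the opposite mechanism as evidence.

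**Uncertainty.** An estimated product is almost never exactly zero. A rule that asks only whether it is positive will be met by chance about half the time when there is nothing to find.

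Mediation is the trial's second specific objective, and the Discussion relies on it to argue for bringing mental health services into primary care. A mediation claim that is reversed, or that rests on chance, would weaken that argument even if the primary comparison is sound.

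**Working it through.** **Plan's own figure.** The article gives no figure for the mediation analysis. Its one design calculation (Sample size {14}: 57% v 73%, 350 randomised 1:1, 80% retained, two-sided 0.05) reproduces:

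- Analysed: 350 × 0.80 = 280, or 140 per arm.
- SE under the null, with pooled proportion 0.65: √(2 × 0.65 × 0.35 / 140) = 0.0570.
- SE under the alternative: √((0.57 × 0.43 + 0.73 × 0.27) / 140) = 0.0562.
- Power = Φ((0.16 − 1.96 × 0.0570) / 0.0562) = 0.805, against 80% stated.

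So 280 is used as the analysed number below.

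**Sign of the hypothesised product.** Let a be the effect of ImpACT+ on the mediator and b the effect of the mediator on the outcome. The hypothesis gives a < 0.

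| Outcome | Higher is | b | a × b | Rule a × b > 0 |
|---|---|---|---|---|
| Viral load | worse | + | − | reversed |
| Missed visits | worse | + | − | reversed |
| Gaps in care | worse | + | − | reversed |
| Viral suppression (yes) | better | − | + | right direction |
| Adherence | better | − | + | right direction |
| Visits kept | better | − | + | right direction |

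Recoding the mediator as a reduction does not help. Both paths change sign (for viral load a > 0, b < 0) and the product stays negative.

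**How often a bare positive product arises.** For one mediator with linear paths and independent estimates,

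P(â·b̂ > 0) = P(â > 0)·P(b̂ > 0) + P(â < 0)·P(b̂ < 0).

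*No mediation.* If either path is zero, its estimate is positive with probability 0.5 and the expression equals 0.5 whatever the other path is. Simulation (280 analysed, 20,000 replicates per scenario) gave 49.9% with both paths null, 49.9% with only a non-zero and 49.7% with only b non-zero. With two independent null mediators, at least one passes with probability 1 − 0.5² = 75%.

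*Hypothesised mechanism true, viral load as the outcome.* The article gives no path sizes, so these are assumptions in SD units. SE(â) = √(1/140 + 1/140) = 0.120 and SE(b̂) ≈ 1/√280 = 0.060.

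- a = −0.4, b = +0.3: P(â > 0) = Φ(−3.35) = 0.0004, and P(b̂ < 0) is negligible. The total is about 0.04% by formula and 0.07% by simulation.
- a = −0.2, b = +0.15: P(â > 0) = Φ(−1.67) = 0.047 and P(b̂ < 0) = Φ(−2.51) = 0.006. Then 0.047 × 0.994 + 0.953 × 0.006 = 5.3% by formula and 5.5% by simulation.

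*Opposite mechanism* (ImpACT+ raises stress, and stress raises viral load; a = +0.4, b = +0.3): the rule is met in 99.97% of simulated trials.

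*Outcome where higher is better* (a = −0.4, b = −0.3): the rule is met in 99.97% of simulated trials, so the direction is right there.

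**With an uncertainty criterion.** Joint significance of both paths at two-sided 0.05, as a simple stand-in for an interval on the product, cuts the false-positive rate per mediator to about 0.3% (both paths null) or about 5% (one null). With the expected sign set to negative, it finds the viral-load mechanism in about 91% of trials for the larger assumed paths and about 28% for the smaller.

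**The case against.** **Viral load may be shorthand for suppression.** The mediation paragraph opens by speaking of effects on the primary and secondary outcomes, and the only primary outcome is binary suppression. Objectives {7} names suppression as the mediated primary outcome, and the Discussion speaks of the likelihood of suppression being mediated. On that reading both paths are negative and the rule points the right way for the primary outcome. This stands. A reader might infer that the rule simply rejects the trial's hypothesised mechanism, and the article does not support anything so general. What survives is the reversal for missed visits and gaps in care, and for viral load if the word is meant as written.

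**The interval may be elsewhere.** This is a condensed article, the sentence cites a method reference, and an analysis plan not shown may attach a bootstrap interval. That is possible, so the 50% figure holds only for the literal reading. But the article states a criterion, and the same section does specify confidence intervals for the primary risk ratio. An interval tested only for lying above zero would also keep the sign fault.

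**The size depends on assumed linear paths.** This is true of the 0.1% to 5.5% range and of the 99.97% figures. It is not true of the 50%, which follows from symmetry about zero.

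**A floor in viral load.** With 57% to 73% expected to be suppressed and an assay limit of 20 copies/mL, a reader might also infer that continuous viral load would pile up at the floor. The article gives no viral-load distribution, being below 50 is not being at 20, and 27% to 43% are expected not to be suppressed. That argument is not relied on here.

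**Conclusion.** The mediation rule is wrongly stated for the set of outcomes it is meant to serve. The hypothesised product is negative for viral load as named, missed visits and gaps in care, and positive for suppression, adherence and visits kept. That conclusion needs only the article's hypothesis and the outcome coding.

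Taken literally, the rule is also met about 50% of the time per mediator when there is no mediation, for any outcome. For viral load it would accept the true hypothesised mechanism in about 0.1% to 5.5% of trials, given 280 analysed, linear standardised paths and assumed sizes of a from −0.2 to −0.4 and b from 0.15 to 0.3.

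It would be wrong to infer that the trial's main result is at risk. Mediation is a secondary hypothesis, the primary risk-ratio analysis does not use this rule, and the sample size calculation reproduces. This should be fixed, but it does not undermine the design.

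**What to change.** Replace the decision sentence in Statistical methods {20a}, or settle the point in the analysis plan before allocation is revealed, along these lines:

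1. Name 12-month viral suppression (below 50 copies/mL) as the mediated primary outcome, in line with Objectives {7}, and use that term throughout the mediation paragraph.
2. For each outcome, state its coding and the expected sign of the indirect effect: positive for suppression, adherence and visits kept; negative for missed visits and gaps in care, and for viral load if it is analysed.
3. Require a 95% bootstrap or Monte Carlo confidence interval for the indirect effect that excludes zero in the stated direction before calling it evidence of mediation.

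The cost is wording and a modest amount of analysis code. No new data, visits or participants are needed, and the primary analysis and sample size stay as they are.
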